### Randomization and blinding

The randomization sequence was generated by the study biostatistician using Stata 15.0 statistical software, with stratification by country. In each country, two sites were allocated to cross into the intervention after 4 months under standard-of-care phase, 2 after 8 months under standard-of-care, and 2 after 12 months under standard-of-care. The allocation sequence remains concealed from all investigators during the first 3 months of the study, so that all sites start under standard-of-care blinded of when the intervention phase will start. Then, the biostatistician discloses to Principal Investigators which four sites in the two countries have been randomized to start the intervention in the first step (see Fig. 2). The four sites undergo a transition phase of 1 month with trainings before crossing to the intervention phase. All other sites continue in the standard-of-care, still blinded on the time when they will start the intervention, until the last month before the next step. The one-month notice given before starting into the transition phase will allow sites to adequately plan for trainings in the study sites.

The study design does not allow the site investigators to be blinded after assignment to interventions.

### Statistical considerations

In a stepped wedge study, exposed (intervention) and unexposed (standard-of-care) observation periods take the place of “arms” in parallel cluster trials. Thus, the distribution of outcomes across unexposed observation periods is compared with that across the exposed observation periods [20, 21].

Characteristics of the individuals and clusters will be summarized by exposure status (intervention versus standard-of-care period) to assess for potential selection biases and lack of balance. These characteristics will also be compared by steps. This will include the numbers analyzed, the average cluster size, cluster characteristics (in terms of TB care cascade), and important patient characteristics (TB treatment outcomes). All comparisons will be performed with a level of significance alpha of 5%.

Following an intention to treat principle, clusters will be analyzed according to their randomized crossover time irrespective of whether crossover was achieved at the desired time. In addition, we will carry on per protocol analyzes where the clusters will be analyzed according to the real timing on which the crossover actually occurred.

Data collected during the one-month transition phase from standard-of-care to intervention will not be considered in the analysis of outcomes, in order to minimize contamination between study periods.

We will estimate the TB detection rates for each cluster during each step. We will then summarize the detection rates by intervention period (standard-of-care versus integration) and display the summaries using graphs. To estimate the effect of integration on TB detection rates (i.e., proportion of cases diagnosed), we will use generalized linear mixed Poisson models. The effect will be presented as rate ratio and associated 95% confidence interval.

We will use time to event survival analysis approaches with frailties to estimate the effect of the intervention on treatment completion. This approach allows us to account for TB patients lost to follow-up or who transfer to other facilities while estimating treatment completion rates. In addition, we will use descriptive analysis to assess the fidelity of the implementation of the intervention over time and secondary outcomes that are likely to be infrequent and thus with limited power to detect differences.

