### Outcomes

The primary outcome is the proportion of children diagnosed with TB defined as the number of pediatric TB cases diagnosed over the number of children attending the child healthcare services during the study period.

Main secondary outcomes include:
Proportion of children screened for TB among the total number of children attending the child healthcare services.Proportion of children diagnosed with TB (bacteriologically or clinically) among presumptive TB cases, overall and disaggregated by HIV status and nutrition status.Time from screening to clinical or bacteriologic diagnosis.Time from diagnosis to treatment initiation.Proportion of cases with a bacteriologically confirmed diagnosis.Treatment outcomes for patients initiated on treatment according to WHO categories, with a focus on treatment completion rate.Cost-effectiveness from a health system perspective, as US dollars per disability-adjusted life-year (DALY) averted.Comprehensive understanding of caregivers’ perceptions and patients’ and communities’ acceptability of receiving integrated pediatric TB services within pediatric care.

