### Sample size

The total number of clusters enrolled in this study has been determined under three assumptions: 1) the expected “sample size” of clusters, which is the number of children seen per month in each cluster; 2) the expected baseline “detection rate”, which is the proportion of cases diagnosed on the total number of children, during the standard-of-care phase; and 3) the “effect size” of the intervention which is the expected increase in detection rate between standard-of-care and intervention phase. According to baseline records, we estimate that the number of consultations in children less than 5 years of age will be at least 500 per month in each cluster. We assume that at least 2 children will be diagnosed with TB per 1000 children attending the child health care services, under standard-of-care. Published studies on interventions to enhance case detection in adults demonstrated an effect of the intervention of 50% [15]. However, it is well known that under-reporting of child TB cases is much more prevalent than adult TB cases [2], and thus we believe it will be more subject to improvement. Indeed, whereas the incidence of TB in children is expected to be 10 to 12% of the total number of TB cases in a particular country, the notified TB cases in children represents only 6% of the total number of TB cases in Cameroon and Kenya. We designed the study according to an expected effect size ranging between 50 and 100%.

Based on a stepped-wedge design, with 2000 children attending consultations during each four-month step of the study, four randomly selected study sites per step and 12 sites in total (three steps in the study), and an ICC correlation of 0.001, we will have 96.5% power to see a doubling in the case detection from two to four per 1000.

With this design and assumptions, we expect to follow 300 confirmed pediatric TB cases during the whole study duration. Current TB treatment completion rates in routine care are estimated at least at 70%. With 96 cases expected under standard-of-care and 192 cases under intervention, the power will be 80% to detect a 20% increase in completion rate.

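### The check for selection bias is built on trial outcomes (care cascade and treatment outcomes), so for outcomes conditional on diagnosis it cannot separate an intervention effect from a change in case mix

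*Protocol article*

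**What the plan says.** The protocol article, under Statistical considerations, plans to summarise individuals and clusters by exposure status, and also by step. The stated purpose is "to assess for potential selection biases and lack of balance". The variables it lists are the numbers analysed, the average cluster size, "cluster characteristics (in terms of TB care cascade") and "important patient characteristics (TB treatment outcomes"). The same paragraph sets a 5% significance level for all comparisons.

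The Outcomes section lists the same kinds of measure as secondary outcomes. One is "Treatment outcomes for patients initiated on treatment according to WHO categories, with a focus on treatment completion rate". Another, from the cascade, is "Proportion of children screened for TB among the total number of children attending the child healthcare services". Times to diagnosis and to treatment start are also there.

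For completion, the analysis is described as follows: "We will use time to event survival analysis approaches with frailties to estimate the effect of the intervention on treatment completion". The reason given for this approach is loss to follow-up and transfer.

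**The concern.** A check for selection bias asks whether the children compared in the two phases were alike before the intervention could act on them. Treatment outcomes and cascade measures arise after exposure and are what the intervention is intended to change. If they differ between phases, that may be effect, selection or both. If they do not differ, a real effect and an opposing shift in case mix may have cancelled.

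The weakness bears on outcomes that exist only for diagnosed or treated children. The intervention package (section on the CaP TB intervention) adds waiting-room screening, a new or strengthened diagnostic algorithm, specimen-collection training, Xpert support and X-ray support. Each can change which children are diagnosed. Two further routes to selection exist: site investigators cannot be blinded once a site has crossed over (Randomization and blinding), and enrolment depends on clinicians notifying the nurse and on caregiver consent (Evaluation activities and data collection processes). A useful balance check is therefore needed, and the variables named for it do not provide one. At stake is whether a difference in completion can be read as better care.

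**Working it through.** **1. The two lists side by side.**

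| Named for the bias check (Statistical considerations) | Status in Outcomes |
|---|---|
| Cluster: TB care cascade | Secondary outcomes (screening proportion, times to diagnosis and treatment) |
| Patient: TB treatment outcomes | Secondary outcome, with completion as its focus |

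Apart from the counts (numbers analysed, cluster size), nothing named is fixed before exposure.

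**2. Expected cases (the plan's own figures).** Inputs from Sample size and Randomization: 12 clusters, four crossing at each of months 4, 8 and 12; four-month steps, so 16 months in all; 500 children per cluster-month; "a doubling in the case detection from two to four per 1000".

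- Standard-of-care cluster-months: 4×4 + 4×8 + 4×12 = 96. Cases: 96 × 500 × 0.002 = 96.
- Intervention cluster-months: 4×12 + 4×8 + 4×4 = 96. Cases: 96 × 500 × 0.004 = 192.

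Both match the document. At the standard-of-care rate, the intervention cluster-months would have yielded 96 cases, so 192 - 96 = 96 are additional, a share of 1/2.

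The document also says "We designed the study according to an expected effect size ranging between 50 and 100" percent. At the lower end, 96 × 500 × 0.003 = 144 cases, of which 48 (1/3) are additional.

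**3. Planned difference in completion.** The document gives 70% completion in routine care and 80% power for a 20% increase, without saying relative or absolute. Two-proportion test, two-sided 5% (sidedness assumed), 96 against 192:

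- relative, 70% × 1.2 = 84%: power 77.6%;
- absolute, 70% + 20 points = 90%: power 98.3%.

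The stated 80% is not reproduced exactly. The relative reading is close (79.2% with 100 and 200 cases), so I take the planned difference as about 84 - 70 = 14 points. The small gap in power does not bear on this point.

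**4. Shift from case mix alone.** Assume no effect on completion for any child, and that children whom standard of care would also have found complete at 70%. With additional share f completing at q (an assumption, not in the document):

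intervention completion = (1 - f) × 70% + f × q.

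| q | f = 1/2 (doubling): completion, shift | Rejects at 5% | f = 1/3 (50% rise): completion, shift | Rejects at 5% |
|---|---|---|---|---|
| 50% | 60%, -10 | 38% | 63.3%, -6.7 | 18% |
| 60% | 65%, -5 | 13% | 66.7%, -3.3 | 8% |
| 70% | 70%, 0 | 5% | 70%, 0 | 5% |
| 80% | 75%, +5 | 15% | 73.3%, +3.3 | 9% |
| 90% | 80%, +10 | 47% | 76.7%, +6.7 | 21% |

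Example: 0.5 × 70% + 0.5 × 90% = 80%. The rejection figures are for a simple two-proportion comparison that ignores clustering. They show scale and do not predict the frailty model.

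**5. What the named check would show.** In every row except q = 70%, a table of treatment outcomes by phase would show the difference and give no means of attributing it to case mix or to care.

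**The case against.** The strongest reply is that the list is open: it says what the summary will include, not what it is limited to. Hypothesis and aims plans to describe children diagnosed with active TB and to determine HIV infection among presumptive and confirmed cases. It also breaks the cascade down by service and level of care. Outcomes splits diagnostic yield by HIV and nutrition status. A reader might infer that a shift in case mix would go wholly unseen. The documents do not support that, because these data could partly reveal one. What stands is that none of them is tied to the bias check or to the completion analysis, and that the variables which are named cannot do the job.

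Three other strong readings also fail.

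- *The completion model ignores case mix.* The article names no covariates, but such lists are commonly left to the full protocol or analysis plan, and an analysis of factors associated with treatment outcomes is foreseen. Silence here is not an error.
- *An effect would be declared an imbalance.* The article attaches no decision rule to the table, and the 5% level is a general statement.
- *Completion would be inflated.* No direction is given. Rationale for the INPUT study names pediatric ART and nutrition rehabilitation services among possible entry points, so integration could raise the share of higher-risk children as well as lower it.

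It may also be said that this is only wording. It is, but the wording gives outcomes the role of baseline characteristics, and no later detail can make them valid for it.

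**Conclusion.** The point holds in a limited form. The variables named for assessing selection bias are trial outcomes and are unsuitable for that purpose wherever an outcome is conditional on diagnosis, above all treatment completion. The primary outcome is not affected in this way, since its denominator is all attending children.

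The possible distortion of completion is -10 to +10 points under the planned doubling and about -7 to +7 under a 50% rise, against a planned difference of about 14. This range rests on assumed completion of 50% to 90% among additional cases, 70% among the others, and the relative reading of the 20% increase. It shows that case mix alone could produce or hide a sizeable part of the planned difference; it is not an estimate of bias. The change should be made: it costs little and supports how a main secondary outcome is read.

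**What to change.** 1. In Statistical considerations, replace the cascade measures and treatment outcomes in the balance summary with characteristics fixed before diagnosis and already collected: age, sex, HIV status, nutritional status, entry point, and hub or spoke. Show them descriptively, without significance tests, by phase and by step, for presumptive and for diagnosed children separately.
2. Report cascade and treatment measures as outcomes only.
3. Report a completion estimate adjusted for age, HIV status and nutritional status beside the crude one, and state that adjustment reduces but does not remove selection on diagnosis. Do not adjust for disease site, because it is established by the work-up that the intervention changes.
4. Optionally, add completions per attending child as a supplementary measure. Its denominator is not selected by diagnosis, but it would mostly follow detection: doubling cases at an unchanged completion rate doubles completions. It cannot replace the adjusted estimate.

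Cost: a wording change and a small analysis of existing data. Some covariate values, HIV status for instance, will be missing, and there is one more estimate to report.

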### Sample collection methods and concomitant care

Sputum and other laboratory specimens such as gastric lavage, induced sputum, nasopharyngeal aspirate and lymph node aspiration are collected from children and processed according to manufacturer protocols and national guidelines.

Specimens are tested using Xpert MTB/RIF assay (Cepheid, Sunnyvale, California, USA). Xpert testing and interpretation of results are carried out according to manufacturer instructions. Sputum smear microscopy is performed following the Ziehl-Nielsen method. At least 100 high power fields will be read before returning a negative result. Results are reported as follows: No acid-fast bacilli seen, exact number of bacilli seen if less than 10 in 100 fields, + if 10–100, ++ if 100–1000, +++ if > 1000 per 100 fields.

Sputum samples for culture are processed according to national standard of care. This is not part of CaP TB project but will be carried out with support from national program.

All children who have positive TB symptoms and who are HIV exposed or whose exposure status is unknown will be screened for HIV with age-specific test. For children who are still breastfeeding or young infants aged less than 12 months, HIV diagnosis will be done using the Cepheid/Alere point of care qualitative test while older children who have stopped breastfeeding for more than 6 weeks will be tested for HIV using rapid test according to national standard of care. All HIV laboratory testing will be performed per the routine MoH protocols.

Treatment of active TB will follow national and WHO guidelines during both the standard-of-care and intervention phase. During intensive phase of treatment and as per the current WHO guidelines the treatment will be dispersible fixed dose combinations of isoniazid-rifampicin-pyrazinamide associated with ethambutol and during the continuation phase the treatment will be isoniazid-rifampicin. The duration of the treatment will depend on the type of TB disease (pulmonary or extra-pulmonary) and will follow national guidelines. Typically, the treatment will last 6 months in pulmonary TB and will extend to 1 year for TB meningitis or osteo-articular meningitis.

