**Fig. 3 Fig3:**
[figure not shown]
INPUT study SPIRIT flow diagram. **a** Allocation done at cluster level prior to enrolment of  participants, according to stepped-wedge design. **b** Ideally, simple TB infection treatment will last for six months, but for TB meningitis, osteo-articular TB or cases that do not respond to treatment appropriately, treatment may be extended to 12 months. All Information on treatment follow-up visits will be recorded as they occur. At least monthly visits will be planned. Information on additional visits, when the child comes for intercurrent illnesses, will also be recorded. **c** If any new results are collected

In both standard-of-care and intervention phases, site clinicians notify the study nurse of all children potentially eligible for enrolment. In addition, the study nurse regularly reviews the existing registers in the sites to extract anonymous screening information about children with presumptive TB: service where seen, age, gender, reason for coming, date of visit. Study nurses approach mothers or caregivers of children who have a diagnosis of presumptive TB on the day of presentation or as soon as possible thereafter to screen the child for eligibility as per inclusion criteria and enroll them after obtaining written consent.

Then, diagnosis, treatment and monitoring activities are scheduled according to the routine of TB care. The study nurse collects data prospectively upon diagnostic work-up (clinical, laboratory and X-ray findings if done). Children are initiated on treatment by the healthcare providers on site and the study nurse prospectively collects data from treatment reports. Similarly, children coming monthly to the study sites for treatment refill are monitored by the healthcare providers as usual, and the study nurse takes this opportunity to collect follow-up data. Ideally, follow-up will continue until 2 months after treatment completion but the maximum follow-up duration is 12–14 months. The duration of follow-up is determined at treatment initiation based on the type of TB diagnosis. However, some reasons may lead to the interruption of monitoring (referral of the child, serious adverse event, death, loss to follow-up). In all cases, the date and reasons for the interruption will be collected in the report form.

Enrolled children who are determined not to have TB are followed during diagnostic procedures then terminated from the study once they are determined not to have active TB.

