### Time period for the study

Participants are planned to be recruited from May 2019 until October2020, and follow-up will be completed by June 2021. Then, results will be analyzed and shared as described in dedicated parts of the protocol, with publications expected end 2021 / early 2022. The study is planned to last for 3 years overall.

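### Treatment completion is analysed as a time to event although a completer's time is largely the planned course length, so the estimate also reflects the mix of 6- and 12-month courses

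*Protocol article*

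**What the plan says.** - **Analysis** (Protocol article, Statistical considerations): "We will use time to event survival analysis approaches with frailties to estimate the effect of the intervention on treatment completion". The reason given is: "This approach allows us to account for TB patients lost to follow-up or who transfer to other facilities while estimating treatment completion rates". The section does not say whether loss is censored or treated as a competing event. It names no covariate or stratum for planned course length.
- **Course length** (Sample collection methods and concomitant care): "Typically, the treatment will last 6 months in pulmonary TB and will extend to 1 year for TB meningitis", with osteo-articular disease named beside meningitis. The Fig. 3 legend gives 6 months as the ordinary course. For meningitis, osteo-articular TB or inadequate response it says "treatment may be extended to 12 months".
- **Follow-up** (Evaluation activities and data collection processes): "The duration of follow-up is determined at treatment initiation based on the type of TB diagnosis".
- **Outcome and power:** Outcomes lists WHO treatment outcome categories with emphasis on the completion rate. Sample size powers completion from 70% with a 20% increase, using 96 cases under standard of care and 192 under intervention.
- **Calendar** (Time period for the study): "Participants are planned to be recruited from May 2019 until October2020, and follow-up will be completed by June 2021".

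**The concern.** In most survival analyses a shorter time to the event means something about benefit or harm. Here it does not. Children who complete a 6-month and a 12-month course have both succeeded, but on a common time scale the second looks slower. The hazard of completion thus mixes how many children complete with how long their courses were meant to be.

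The children analysed are those diagnosed, and diagnosis is what the intervention acts on. It adds waiting-room screening, a diagnostic algorithm in primary care and training in further sampling methods. Detection is expected to rise by 50 to 100%. Disease type among the cases is therefore not protected by randomisation. A frailty, presumably at cluster level, is not designed to absorb a child-level difference in planned course.

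At stake is a named secondary outcome: a difference in completion could be reported, hidden or reversed with no change in the share of children completing.

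**Working it through.** **1. The plan's own figures point to a proportion.**
Cases: 500 children a month × 4 months = 2,000 per cluster and step. Standard of care: 4 clusters × (1+2+3) steps × 2,000 × 0.002 = 96. Intervention: 4 × (3+2+1) × 2,000 × 0.004 = 192. Both match the protocol.

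Power for two proportions, 70% versus 84% (20% read as relative), two-sided 5% (sidedness assumed):
- pooled p = (96×0.70 + 192×0.84)/288 = 0.793
- SE under the null = √[0.793×0.207×(1/96+1/192)] = 0.0506
- SE under the alternative = √[0.70×0.30/96 + 0.84×0.16/192] = 0.0537
- z = (0.14 − 1.96×0.0506)/0.0537 = 0.76, so power is 77.6%

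The stated 80% is not reproduced exactly. The rounded total of 300, split 100:200, gives 79.2%. An event-based calculation (HR = ln 0.16/ln 0.30 = 1.52; 228 events) gives 84.9%, and an absolute rise to 90% gives 98.3%. So 80% looks like a rounded, unclustered comparison of proportions.

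**2. Effect of the mix when completion is equal.**
From the documents: planned courses of 6 or 12 months; 70% completion. Assumed: the long-course shares; completers finish at the planned end plus a half-normal delay (scale 0.5 month); non-completers leave uniformly over the planned course; no cluster frailty. Cox models were fitted to 6,000 standard-of-care and 12,000 intervention children (simulation SE of the log HR about 0.02). The true effect is nil.

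| Long-course share, standard of care → intervention | Losses censored: unstratified HR | Losses censored: stratified HR | Non-completers kept at risk: unstratified HR |
|---|---|---|---|
| 10% → 10% | 0.99 | 1.00 | 1.03 |
| 5% → 10% | 0.87 | 1.00 | 0.98 |
| 5% → 15% | 0.77 | 1.02 | 0.92 |
| 10% → 20% | 0.76 | 1.01 | 0.94 |
| 20% → 10% | 1.28 | 1.00 | 1.03 |

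With a uniform delay of 0 to 0.5 month and losses censored, 20% → 10% gives 1.29, 10% → 5% gives 1.17 and 15% → 5% gives 1.35. With non-completers kept at risk, that setting gives 1.04 to 1.09. With no losses at all, 20% → 10% gives about 1.23 and 5% → 15% about 0.78, so the mechanism does not depend on loss.

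**3. What the shifts mean in cases.**
- 20% → 10%: 0.20×96 = 19 and 0.10×192 = 19 long courses, so every added case has a short course.
- 5% → 10%: 4.8 and 19.2, so 14.4 of the 96 added cases (15%) have long courses.
- 5% → 15%: 4.8 and 28.8, so 24 of 96 (25%).
- 15% → 5%: 14.4 and 9.6, which needs a fall in the number of long courses.

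**4. Size at trial scale.**
Completions: 96×0.70 ≈ 67 and 192×0.70 ≈ 134. SE of the log HR = √(1/67+1/134) = 0.15. An HR of 0.77 has log −0.26, or 1.7 SE. In 300 simulated trials of 96 and 192 children without clustering, the 5% → 15% shift with losses censored led the unstratified test to reject in about 46% of trials, against 4% when stratified. With non-completers kept at risk the unstratified test rejected in 6%.

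**5. Stratification alone is not enough.**
With a real gain from 70% to 84%, no shift in mix and losses censored, the HR is 1.04 unstratified and 0.99 stratified. Children who stop have left the risk set before the planned end, so those remaining are almost all completers in both phases. With non-completers kept at risk the HR is 1.44 unstratified and 1.46 stratified.

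**6. Calendar.**
October 2020 to June 2021 is about 8 months. A 12-month course begun after about June 2020 cannot be seen to finish, whereas a 6-month course begun in October 2020 can. The last sites are due to cross after 12 months of a study begun in May 2019, so these truncated long courses fall essentially in the intervention phase.

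**The case against.** The strongest reply is that the article does not specify the model simulated here. It names no Cox model, single baseline hazard, censoring rule or hazard ratio for completion, and strata and covariates for a secondary outcome normally belong in an analysis plan, which is not shown. This stands in part. A reader might infer that the protocol pools the course types; the text neither says so nor rules it out. What the protocol does fix is the time-to-event scale, and that is where the difficulty arises.

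The reply is also right that no long-course share is given, that no shift is predicted, and that the larger distortions require losses to be censored, which is only one reading of the text. It is right, too, that stratifying with losses censored would leave almost no power for the planned effect. That changes the remedy; it does not remove the problem.

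The planned summaries of patient characteristics by phase, and the description of diagnosed children, could reveal a change in disease type. They would not correct the estimate. Finally, the Fig. 3 legend allows extension for inadequate response, so course length is not wholly fixed at the start. The protocol says that follow-up duration is set at treatment initiation, not that planned treatment duration is a recorded field.

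**Conclusion.** The point holds in limited form. A time-to-completion estimate reflects the mix of planned durations as well as the share completing, and the design does not balance that mix. Under assumed shifts of 5 to 10 points with equal 70% completion, an unstratified HR is roughly 0.8 to 1.3 if losses are censored and 0.9 to 1.1 if non-completers stay at risk. These figures rest on assumed shares, an assumed pattern of stopping and no clustering.

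Two stronger readings are not supported. One is that the hazard ratio would measure only regimen mix: it would also respond to completion if non-completers stay at risk. The other is that the intervention will shift the mix in a known direction: the documents do not say so.

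The measure also does not match the plan's own target, since outcome and power are stated as a completion proportion.

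**What to change.** - **Main completion analysis:** compare the proportion of treated children who complete by their own planned end of treatment plus a fixed, prespecified window, with loss counted as non-completion and a cluster random effect. This matches the Outcomes and Sample size sections.
- **If the time-to-event model is kept:** stratify the baseline hazard by planned duration as set at treatment initiation, and keep non-completers in the risk set (competing-event handling) instead of censoring them.
- **Reporting:** tabulate planned duration by phase. State beforehand how transfers are classed, and how children are handled whose planned end plus window falls after June 2021.

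The cost is a short specification and a little more analysis work. Planned duration must be derived from the TB type recorded at treatment start, so later extension for inadequate response should not reclassify a child. No new data collection should be needed.

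### The survival model for treatment completion, read in the ordinary way, censors children lost to follow-up; that overstates completion, shrinks the difference between phases, and leaves the stated 80% power without a matching analysis

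*Protocol article*

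**What the plan says.** The Outcomes section lists among the main secondary outcomes: "Treatment outcomes for patients initiated on treatment according to WHO categories, with a focus on treatment completion rate". The population is therefore children started on treatment, and the quantity is the rate at which they complete.

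The Sample size section puts routine completion at 70% or more and continues: "With 96 cases expected under standard-of-care and 192 cases under intervention", "the power will be 80% to detect a 20% increase in completion rate". No other secondary outcome has a power statement.

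Statistical considerations sets the analysis: "We will use time to event survival analysis approaches with frailties to estimate the effect of the intervention on treatment completion". The reason follows directly: "This approach allows us to account for TB patients lost to follow-up or who transfer to other facilities while estimating treatment completion rates". No competing-event method is named, and nothing says that a lost child counts as not having completed.

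On course length, the section on sample collection and concomitant care says: "The duration of the treatment will depend on the type of TB disease (pulmonary or extra-pulmonary) and will follow national guidelines". It gives 6 months as typical for pulmonary disease and up to 1 year for certain other forms. The section on evaluation activities lists referral, serious adverse event, death and loss to follow-up as reasons monitoring may stop, and says that dates and reasons are recorded.

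**The concern.** Completion can be reached only at the end of a course whose length is set in advance. A child lost in month 3 of a 6-month course has not completed. Censoring that child assumes the same chance of completing as a child who stayed in care, so the failures that the outcome is meant to count leave the calculation. What remains is mostly a comparison of when the retained children reach their last visit.

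Two things follow. First, a real improvement in retention can be understated or missed. Better treatment outcomes are part of the trial's stated hypothesis, so this matters. Second, because course length differs by disease type, an intervention that changes which forms of TB are found can move a hazard ratio for completion even when the proportion completing is unchanged.

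**Working it through.** **Inputs from the article.** 70% completion under standard of care; 96 and 192 cases; 20% increase; 80% power; 5% significance level (two-sided assumed). Not given: the share *f* of non-completers who would be censored, and the mix of course lengths. Both are shown as ranges.

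**Step 1: the case counts.** Standard of care: 4 sites × (4 + 8 + 12) months = 96 site-months; 96 × 500 × 0.002 = 96 cases. Intervention: 4 × (12 + 8 + 4) = 96 site-months; 96 × 500 × 0.004 = 192 cases. Both reproduce.

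**Step 2: the stated power.** Take 20% as relative, 0.70 × 1.2 = 0.84, in a two-proportion test with all cases in the denominator:
- pooled proportion (96 × 0.70 + 192 × 0.84)/288 = 0.793
- null SE √[0.793 × 0.207 × (1/96 + 1/192)] = 0.0506
- alternative SE √(0.70 × 0.30/96 + 0.84 × 0.16/192) = 0.0537
- power Φ[(0.14 − 1.96 × 0.0506)/0.0537] = Φ(0.76) ≈ 77.6%

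The exact power of the chi-square test is 78.4%, and the formula gives 79.2% at 100 versus 200 cases. An absolute rise to 90% would give about 98%. The stated 80% is therefore a power for proportions on the relative reading, and children lost sit among the 30% who do not complete.

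**Step 3: what a censoring analysis estimates.** If non-completers leave before the end of the course and a share *f* of them is censored, with the same *f* in both phases, estimated completion is p / [p + (1 − p)(1 − f)].

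| f | Standard of care | Intervention | Difference (points) |
|---|---|---|---|
| 0 | 70.0% | 84.0% | 14.0 |
| 0.25 | 0.70/0.925 = 75.7% | 0.84/0.96 = 87.5% | 11.8 |
| 0.50 | 0.70/0.85 = 82.4% | 0.84/0.92 = 91.3% | 9.0 |
| 0.75 | 0.70/0.775 = 90.3% | 0.84/0.88 = 95.5% | 5.1 |
| 1 | 100% | 100% | 0 |

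**Step 4: power of the survival comparison.** Simulated with 96 versus 192 children and true completion of 70% versus 84%. Assumptions: 6-month course, exponential delay to recorded completion with mean 0.5 month, departures uniform over the course, non-completers who are not censored kept in the risk set, no clustering or calendar trend. The right-hand column uses a second timing assumption: completion at weeks 26 to 30 and losses over weeks 1 to 25.

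| f | Power | Power, second timing |
|---|---|---|
| 0 | 70% | 66% |
| 0.25 | 55% | 54% |
| 0.50 | 41% | 36% |
| 0.75 | 20% | 17% |
| 1 | 5% | 5% |

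A comparison of proportions on the same children has about 78% throughout.

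**Step 5: case mix.** Set true completion at 70% in both phases and let the share on 12-month courses differ (assumed values). With all non-completers censored, false rejection is about 18% at 10% versus 5%, and about 50% (hazard ratio about 1.35) at 15% versus 5%. With half censored it is 6% to 12%.

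**The case against.** The article never uses the words censor, Cox or hazard ratio. Time-to-event methods include competing-event models and models with attrition as the event, and the detailed rule may stand in an analysis plan that is not shown. This has force: the class of methods is not blind to the effect. With non-completers kept in the risk set, power is about 70%; with attrition as the event, it is about 78%. What does not fall away is that the article states both the approach and the reason for it, and that reason is the ordinary argument for censoring. It also powers a different quantity.

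A reader might infer that the analysis must report completion near 100% in both phases and hide any effect. That holds only if every non-completer is censored, deaths and failures included. The sentence names only loss and transfer, and the article does not give their share of non-completion.

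A reader might also infer that a false positive is likely through case mix. The 50% figure needs an assumed 15% versus 5% split together with full censoring. It drops quickly under milder assumptions, and stratifying by course length would deal with it.

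Two further points stand. Censoring transfers is easier to defend than censoring loss. Incomplete follow-up of late starters is also a legitimate reason to want a time-to-event method.

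**Conclusion.** The concern holds in a limited form. On its ordinary reading, the planned model treats loss to follow-up as uninformative for an outcome in which loss is itself a failure. It therefore overstates completion and shrinks the contrast. The 80% power belongs to a two-proportion comparison and cannot be carried over.

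If half of the non-completers are censored, the 14-point difference is estimated as about 9 points, and power is about 41% rather than 78%. Total masking is the end of the range, not the expected result. These figures assume the same censored share in both phases, departures spread over the course, and no clustering, so they compare analyses and do not forecast the trial's power. The case-mix effect is real in direction, but its size rests on assumed mixes.

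This should be fixed. It affects one of eight main secondary outcomes and leaves the primary outcome untouched.

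**What to change.** In Statistical considerations, define completion as a binary outcome among all children started on treatment, with loss to follow-up, death and failure counted as not completed. Analyse it in a mixed model with a cluster random effect, calendar period and country. These terms need writing out, because the article's description of the primary model names only a generalized linear mixed Poisson model. Treat transfer-out as not evaluated, with a best-case and worst-case sensitivity analysis.

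If a time-to-event analysis is kept, use cumulative incidence with loss, death and failure as competing events, stratified by planned course length. Censor only for transfer and for the administrative end of follow-up.

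Do not simply drop children whose planned treatment end falls after follow-up closes. Follow-up ends in June 2021, so 12-month courses begun after about June 2020 would go. Enrolment began in May 2019 and the last sites are due to cross after 12 months, so those children belong mainly to the intervention phase. Apply the same eligibility by course length in both phases, or censor these children administratively.

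In Sample size, say that the 80% refers to a comparison of proportions and that the 20% increase is relative, if that is what was meant.

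The cost is a rewritten paragraph and slightly more analysis work. Dates and reasons for interruption are already collected.
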